### 9.4 EXCLUSION CRITERIA

1. Known allergy or hypersensitivity to the components of the investigational product
2. History and/or presence of clinically significant condition/ disorder (self-reported), which per investigator's judgement could interfere with the results of the study or the safety of the subject, e.g.:
  - Nasal disorder (e.g. polyposis, relevant septal deviation, ulcer etc.) and/or reconstructive surgery
  - Acute/chronic airways disease/disorder (e.g. chronic obstructive lung disease, asthma, chronic cough of any origin)
  - Acute psychiatric disorders
  - Any other acute/chronic serious organ or systemic diseases
3. Influenza vaccination within the last 3 months prior to V1 and during the study
4. Regular use of products that may influence the study outcome (e.g. immune suppressants/immune stimulants including natural health products, analgesics/anti-

rheumatics, anti-phlogistics, antitussives/expectorants, mouth or throat therapeutics, decongestants, antibiotics, anti-histaminergic drugs, nasal drops/spray) within the last 4 weeks prior to V1 and during the study (except for the defined optional care)

5. Pregnancy or nursing
6. History of (in the past 12 months prior to V1) or current abuse of drugs, alcohol or medication
7. Participation in the present study of a person living in the same household as the subject
8. Inability to comply with study requirements according to investigator's judgement
9. Participation in another clinical study in the 30 days prior to V1 and during the study

## **9.5 WOMEN OF CHILD BEARING POTENTIAL**

Female subjects may not be pregnant at the time of inclusion into the study. Therefore, pregnancy testing will be performed during screening for women with child bearing potential (women of non-childbearing potential are defined as those who either have no uterus, or have undergone ligation of the fallopian tubes, or have permanent cessation of ovarian function due to ovarian failure or surgical removal of the ovaries, or are in the postmenopause as per investigator's judgement). During the informed consent process, the investigator will advise every woman with child bearing potential that she must use medically recognised contraception during the study duration. In case pregnancy occurs, the subject has to withdraw. Any pregnancy during the study must be notified in writing to the sponsor and the project manager of the CRO by the investigator within 24 hours after their awareness of the event by sending the respective form to:

[name], PhD;

[contact], email: [contact]

[name];

[contact], [contact]

Initial report must be followed up by a detailed written report.

## 10 CLINICAL INVESTIGATION TREATMENT

### 10.1 THE INVESTIGATIONAL STUDY DEVICE

CMS016317 is ColdZyme® Mouth Spray, a Class I medical device (CE-marked) under Council Directive 93/42/EEC on Medical Device and MED-DEV Guidance Document 2.4/1. Rev 8, June 2010; with the following composition: glycerol, water, cod trypsin, ethanol (<1 %), calcium chloride, trometamol and menthol.

ColdZyme® Mouth Spray consists of a 20 ml bottle, pump, spray nozzle and protective cap. A thin plastic label is added to the bottle.

### 10.2 DOSAGE AND USE OF IP

The spray should be applied every second hour up to 6 times with each time 2 puffs (1 dose) per occasion. At V1, the subject will be instructed on the use and the application demonstrated.

[figure not shown]

Figure 2: Application of spray

Depending on the timepoint of treatment onset, there may be less IP applied on the first day of use.

The IP use should start when following conditions have been fulfilled:

- answering "Yes" to either of the questions in the subject diary: "Do you think/feel you have a cold?" or "Do you think/feel you are coming down with a cold (might be having first signs of cold)?"
- Jackson score of at least 1 (mild = sensible, but not disturbing or irritating) for any symptom except headache

The IP should be used until 2 days after the subject is symptom free (=answering "No" to the question "Do you think that you are still sick with this respiratory infection?" for 2 days in a row), but not longer than 12 days in total.

### **10.3 PRODUCTION, PACKAGING AND LABELLING OF IP**

Production and packaging of the IP will be taken over by the sponsor, Enzymatica AB. Labelling will be provided by analyze & realize GmbH.

The labels will contain the following information (in German):

- Random code
- Sponsor: Enzymatica AB, [name]
- CRO: analyze & realize GmbH, [name], [contact]
- Name of the investigational product: CMS016317
- Batch number:
- Dosage: every second hour up to 6 times with each time 2 puffs (1 dose)
- Content per package:
- Expiry date:
- Study code: 016317
- "For clinical study use only"
- Store at room temperature up to maximally 25 °C
- Keep out of reach of children

### **10.4 STORAGE, INVENTORY, RETURN, TRACEABILITY AND DOCUMENTATION OF THE INVESTIGATIONAL PRODUCT**

The investigational product will be provided to the CRO by the sponsor. The CRO will be responsible for storing the investigational product in a proper place, inaccessible to unauthorized persons.

The CRO will distribute the investigational product to the investigator who will hand it out to the subjects. The investigators will be responsible for storing the IP at the appropriate conditions and inaccessible to unauthorized persons. The investigators will only dispense IP to subjects enrolled in this clinical investigation.

The IP should be stored at room temperature up to maximally 25 °C. Exposure to higher temperature (max 37 °C), e.g. to carry the product in a pocket is tolerated for a maximum of 24 accumulated hours throughout the study period. Subjects are not allowed to carry the IP in a pocket of a clothing piece that may be expected to get a temperature close to the body temperature (e.g. trousers, skirt).

Used IP will be collected from the subjects and the IP accountability (per vial weight) will be performed. After completion of the investigation, the empty and unused portion of the IP (if any) will be returned to the CRO and the unused IP either returned to the sponsor or destroyed (as per agreement with the sponsor).

### **10.5 METHODS OF RANDOMISATION AND BLINDING**

The clinical investigation will be conducted in a single-blind randomised manner. The subjects will be randomised at the screening visit. The randomisation list will be provided to the sponsor's assigned responsible person (not involved in the study) by the statistician responsible for generation of the randomisation list. The ratio of randomisation between the "IP group" (IP, and optional care as needed) and the "peer-group" (optional care only, no IP) will be 1:1. Random numbers will be assigned to the subjects in a sequential order based on time of random-

isation at each investigational site (several whole blocks will be allocated to each centre). Randomisation list will be concealed to the investigational sites. It will be stored under lock and key by the sponsor until database closure. After database closure and sign-off of the statistical analysis plan, the sponsor's responsible person will provide the randomisation list to the project manager at the CRO and the statistician responsible for the statistical analysis. The study allows for stratification with respect to centres (sites).

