| Proposed start of the study (first subject in): | Q1 2018                                                                                                                                                                                                                                                                                                                                                                                                                                                                                                                                                                                                                                                                                                                                                                                                 |
| Proposed end of the study (last subject out):   | Q1 2019                                                                                                                                                                                                                                                                                                                                                                                                                                                                                                                                                                                                                                                                                                                                                                                                 |
| Visit schedule:                                 | At screening visit (V1), eligible subjects will be randomised to two groups, the verum group and the "optional care only / no IP" group. All subjects will get the subject diary.

The subjects in the verum group have to use the IP as defined and may use optional care (see the definition in the "Duration of intervention" below) as needed in accordance with the definition of optional care. The subjects in the "optional care only / no IP" group do not receive any IP and may use optional care as needed in accordance with the definition of optional care.

Within maximally 3 days after answering "yes" to the question on common cold and the onset of at least mild symptom(s) in Jackson scale (see "Duration of intervention") (for both study groups) as well as the |

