## **12 CONDUCT OF THE CLINICAL INVESTIGATION**

### **12.1 VISIT 1 (V1, SCREENING, RANDOMISATION)**

- Oral and written information about the nature, purpose, possible risks and benefits of the study provided to the subjects by the investigator
- Written consent of the subject to participate; the subject understands the requirements of the clinical investigation and is willing to comply
- Questioning and documentation of the medical history, concurrent diseases and treatment, demographic and anthropometric data, and physical examination by the investigator
- Verification that the inclusion criteria are met and that there are no violations of the exclusion criteria
- Measurement of blood pressure and pulse rate
- Urinalysis and pregnancy test (for women with childbearing potential)
- Issue of subject diary and instruction for recording
- Randomisation
- Issue of IP (verum group) and instruction for use
- Questioning and documentation of possible occurrence of adverse events (AEs)

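### Random codes on verum-only packs, used in sequence and stored at the site, would defeat the stated concealment if packs arrive coded; if they do not, the protocol gives the site no way to learn the arm at V1

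*Protocol*

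**What the plan says.** **Sequence and custody (Protocol 10.5).** Allocation is 1:1. "Random numbers will be assigned to the subjects in a sequential order", by time of randomisation within each site, and "several whole blocks will be allocated to each centre". On secrecy: "Randomisation list will be concealed to the investigational sites", and "It will be stored under lock and key by the sponsor until database closure". The project manager at the CRO and the analysis statistician receive the list only after database closure and SAP sign-off.

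**Who gets a pack.** The V1 list in 12.1 includes "Issue of IP (verum group) and instruction for use". For the comparison arm, the Synopsis says that subjects in that "group do not receive any IP and may use optional care as needed". No dummy pack or empty container is described.

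**Labels and storage.** Section 10.3 names the random code as the first label item and states: "Labelling will be provided by analyze & realize GmbH". Under 10.4 the CRO distributes the IP to the investigator, and investigators store it and hand it out.

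**Blinding (10.6).** Subjects, site staff who handle IP, and monitors know the arm. The investigator who assesses the cold at V2 and the project manager do not.

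**The concern.** Locking up a list conceals allocation only if nothing else at the site reproduces it. Here the coded packs may do so: a code with a pack is a verum allocation, and a code without one is a control allocation. Staff who can foresee the next arm can influence who is enrolled and when. Entry leaves room for that. A history of colds is self-reported (9.2, criterion 3), and ability to comply is left to the investigator's judgement (9.4, criterion 8).

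Concealment matters more than usual in this trial. Subjects are unblinded and the symptom and quality-of-life scales are self-rated, so balanced entry is one of the few protections left. The study's aim is to compare assessments by the size of the treatment effects they show (7.1, 14.1.1), so a biased effect goes straight to its purpose.

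The same leak could reach the V2 assessor. The CRF identifies subjects by screening and randomisation number (17.2), and the V2 judgement feeds the endpoint on prevention of a cold outburst (12.7.1).

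**Working it through.** The protocol gives no figure on concealment, so there is none to reproduce. The check takes the two possible readings of 10.3 in turn.

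**Reading A: packs reach the site already coded.**
- Expected codes: 300 randomised (Synopsis, 9.1). At 1:1, 300 × 0.5 = 150 codes have a pack and 150 have none.
- Rule: if the next sequential code is on a pack, predict IP; if it is missing, predict control.
- Each code has a pack if and only if it is verum, so the rule is right for 100% of the codes covered by the stock on site, whatever the block size. A simulation of 1,000 lists of 300 (block size 4 assumed) gave 1.0, as it must.
- Those able to apply the rule include the investigators, because 10.4 has them store and hand out IP. That does not fit with 10.6, which blinds the investigator who assesses colds at V2.

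**Reading B: the code is added at dispensing.**
- The shelf then reveals nothing.
- But staff must know at V1 whether to issue IP (12.1), while the list is with the sponsor until database closure (10.5). No envelopes, central or web release, or site copy are described. As written, the V1 step cannot be carried out.

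**The CRO's position.** To put the right codes on verum packs only, whoever labels needs to know which codes are verum. Labelling is the CRO's task (10.3), yet its project manager is blinded (10.6) and receives the list only after database closure (10.5). The protocol does not say who at the CRO would hold the codes.

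**What remains once the shelf is silent.** Staff who handle IP know past allocations (10.6). If they also know the block size, they can guess the arm with more places left in the block, with ties at 1/2. For a 1:1 block of size 2m the expected number of correct guesses is

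m + 2^(2m−1) / C(2m, m) − 1/2,

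and dividing by 2m gives the share correct. The block size is not stated, so 2 to 10 is assumed:

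| Block size | Expected correct guesses | Share correct |
|---|---|---|
| 2 | 1 + 2/2 − 0.5 = 1.500 | 75.0% |
| 4 | 2 + 8/6 − 0.5 = 2.833 | 70.8% |
| 6 | 3 + 32/20 − 0.5 = 4.100 | 68.3% |
| 8 | 4 + 128/70 − 0.5 = 5.329 | 66.6% |
| 10 | 5 + 512/252 − 0.5 = 6.532 | 65.3% |

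If the next allocation cannot be inferred at all, the share is 50%.

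**The case against.** The strongest reply is that the protocol never says when the random code goes on the label. Section 10.3 reads like a template, with batch number, content and expiry date left open, and the list custody in 10.5 suggests that the CRO could not pre-code the packs. Site-filled labels would remove the leak. This stands: the 100% figure belongs to reading A only. A reader might infer that every allocation is predictable as a matter of fact, or that the labelling and the concealment can never both hold. The documents do not support either, because a code written at dispensing would satisfy both.

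The reply does not dispose of the point. Under reading B the gap moves to how the arm is released at V1. That is trial conduct rather than analysis, so a SAP would not be expected to supply it.

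Second, 12.1 lists consent and eligibility checks before randomisation, and 15.6 gives random numbers only to subjects who meet the criteria. That order is right, but it does not protect against someone who already knows the next arm while judging eligibility. It is fair to add that nothing in the text says the person judging eligibility looks at the stock. Steering is possible, not shown.

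Third, this is an exploratory pilot without confirmatory claims (14.1.2). That lowers the severity, but it does not make a biased effect size useful.

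**Conclusion.** The point holds in conditional form. Either the coded verum-only packs reproduce the concealed list at the site, or the protocol omits the step by which the site learns the allocation. Under both readings 10.3, 10.4, 10.5, 10.6 and 12.1 must be reconciled.

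Under reading A, prediction is 100% for the codes in stock, assuming packs are coded before shipment and controls have no container. With the shelf closed it falls to about 65–75% if past allocations and a block size of 2 to 10 (assumed) are known, and to 50% if nothing can be inferred.

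A reader might want to turn this into a bias on the endpoints. If a share s of each arm were swapped, and those subjects differed by d standard deviations, the arms would differ by 2 × s × d under no effect. The documents give neither s nor d, so no size can be derived and none is claimed. Severity: should be fixed before the first subject is randomised, since selection at entry cannot be reliably repaired in the analysis.

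**What to change.** - **10.5:** State that each allocation is released only after consent, eligibility sign-off and entry of the number in a log. One way is sequentially numbered, sealed opaque envelopes prepared by the statistician who generates the list or by the sponsor's list holder.
- **10.3:** Replace the random code on the IP label with a kit number unrelated to it, recording the link at dispensing. The CRO can then label without the list. Indistinguishable numbered containers for both arms would serve equally.
- **10.5:** State that block sizes are not disclosed to sites.
- **10.4 and 10.6:** Reconcile who stores and hands out IP with the blinding of the V2 assessor.

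Cost: about 300 envelopes (one per expected subject), relabelling of the packs, and protocol wording. No extra visits or assessments are needed.

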## **10.6 BLINDING**

In this single-blind study, the subjects, the study site staff handling the IP and the study monitors will not be blinded to treatment assignment. The investigator performing the cold symptom assessment at V2, the project manager, the statistician and all further study team members will be blinded to treatment assignment.

The unblinded site study staff and the monitor(s) will take utmost care not to unblind the investigator performing the cold symptom assessment at V2 or any further blinded study team members at any occasion during the entire study duration.

The subjects will be instructed not to unblind the investigator.

## 11 CONCURRENT TREATMENT

The subjects report the concurrent treatment (e.g. other medical devices, medication, any natural health products including food supplements etc.) to the investigator at the first visit. The investigator documents the following information in the CRFs: substance (only for treatment), dosage (only for treatment), start and duration, reason. Subjects will also be advised to inform the investigators of any treatment performed throughout the clinical investigation period.

During the study, the use of any concurrent treatment according to exclusion criteria is not allowed:

- Influenza vaccination within the last 3 months
- Regular use of products that may influence the study outcome (e.g. immune suppressants/immune stimulants including natural health products, analgesics/anti-rheumatics, anti-phlogistics, antitussives/expectorants, mouth or throat therapeutics, decongestants, antibiotics, anti-histaminergic drugs, nasal drops/spray) (except for the defined optional care)

At enrollment, the investigator informs the subjects that any concomitant treatment that could possibly influence the outcome of the study is not allowed, except for the defined optional care.

The following treatment is defined as optional care to be applied as needed during the common cold period:

- paracetamol (max. 2 g/day)
- ibuprofen (max. 400 mg/day)
- sea water nose drops or nose spray
- antibiotics (in case they are necessarily required).

## **12 CONDUCT OF THE CLINICAL INVESTIGATION**

### **12.1 VISIT 1 (V1, SCREENING, RANDOMISATION)**

- Oral and written information about the nature, purpose, possible risks and benefits of the study provided to the subjects by the investigator
- Written consent of the subject to participate; the subject understands the requirements of the clinical investigation and is willing to comply
- Questioning and documentation of the medical history, concurrent diseases and treatment, demographic and anthropometric data, and physical examination by the investigator
- Verification that the inclusion criteria are met and that there are no violations of the exclusion criteria
- Measurement of blood pressure and pulse rate
- Urinalysis and pregnancy test (for women with childbearing potential)
- Issue of subject diary and instruction for recording
- Randomisation
- Issue of IP (verum group) and instruction for use
- Questioning and documentation of possible occurrence of adverse events (AEs)

### **12.2 VISIT 2 (V2), 1– 3 DAYS AFTER SYMPTOM START**

- Questioning and documentation of possible occurrence of AEs/device deficiencies
- Questioning and documentation of new or changed concurrent treatment
- Review of the diary by a study team member (except investigator)
- Assessment and documentation of cold
- Checking criteria for further participation
- Physical examination
- Measurement of blood pressure and pulse rate

Between V1 and V2, the study site will have monthly phone contact with the subjects as a reminder about the study.

### **12.3 VISIT 3 (V3, FINAL), 16 +/-4 DAYS AFTER SYMPTOM START**

- Questioning and documentation of possible occurrence of AEs/device deficiencies
- Questioning and documentation of new or changed concurrent treatment
- Return and control of the subject diary by a study team member (except investigator)
- Return of IP (verum group) and accountability
- Physical examination
- Measurement of blood pressure and pulse rate

- Global evaluation of efficacy by subjects (4-point categorical scale)
- Global evaluation of safety and tolerability by subjects (4-point categorical scale)

## **12.4 TERMINATION VISIT (TV) FOR SUBJECTS WITH NO SYMPTOMS DURING THE STUDY PERIOD, 16 WEEKS +/-7 DAYS AFTER V1**

- Questioning and documentation of possible occurrence of AEs
- Questioning and documentation of new or changed concurrent treatment
- Return of the subject diary
- Return of IP (verum group)

## **12.5 DEMOGRAPHIC AND ANTHROPOMETRIC DATA**

The subject's age (years), gender (male/female) and ethnicity will be assessed and documented in the CRF at V1.

## **12.6 MEDICAL HISTORY / CLINICAL EXAMINATION**

At V1, the subject will be questioned by the investigator regarding the medical history and will undergo a clinical examination. Known pre- or co-morbidities as well as any abnormal and/or pathological findings of the examination will be systematically recorded.

A dipstick urinalysis for the assessment of glucose and proteins and a pregnancy test in women with childbearing potential will be performed.

